#### Data collection tools

The KTE Survey was developed through the Canadian Partnership Against Cancer and is based on a tool developed by Skinner [30]. The survey includes items about the participants’ demographics (e.g., role, designation, organization type, province) and degree of agreement with statements that the information was relevant and useful, increased knowledge, and that stated learning objectives were met. There are also items asking whether the participant plans to discuss the information provided at the session with colleagues or use the information to make changes in practice.

The Education Roll-Out Report was developed by the study team to collect the number of times each EPEC®-Pediatrics module was offered along with the total number of attendees at the session and whether the session was held within the hospital or in the community. Regional Teams will be asked to comment on any successes and challenges in delivering the modules, indicate any ways that the study team could provide additional supports to assist in delivery of the modules and to describe plans for delivery of sessions in the coming quarter.

#### Data analysis

Information obtained through the Education Roll-out Report and the KTE Surveys will be summarized descriptively. Our dissemination goal is to have a minimum of 5 Master Facilitators, 45 Trainers, and 600 End-Users from multiple professional groups across Canada (see Fig. 1) take part in at least one EPEC®-Pediatrics session. Our hypothesis is that the Trainers and End-Users will indicate that the sessions were useful, improved their knowledge related to the topic presented, and had some impact on their practice. We will compare the summarized responses to the Educational Report and KTE Surveys with these goals and hypotheses to determine if they have been achieved.

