#### Sample and procedure

The EPEC®-Pediatrics roll-out will include training of five Master Facilitators within Canada; Master Facilitators are individuals qualified to train future EPEC®-Pediatrics Trainers at the face-to-face conference. There are 3 steps to becoming a Master Facilitator: 1) become an EPEC®-Pediatrics Trainer by completing all 19 online modules and attending a face-to-face conference as a participant; 2) attend a Professional Development Workshop offered by EPEC for additional development of teaching skills, and finally 3) teach at an EPEC®-Pediatrics Train-the-Trainer conference where feedback is provided on teaching skills by existing Master Facilitators. At each of the 16 participating sites, 3 to 5 health professionals will be identified as Regional Team members. Each Regional Team member (*n* = 45-80) will become an EPEC®-Pediatrics Trainer through completion of 19 online-modules and 5 face-to-face modules. Two face-to-face sessions will be held over two full days with the content delivered by the new Canadian Master Facilitators in conjunction with the original developers of EPEC®-Pediatrics. Regional Teams will complete the online modules on their own, then attend one of the two-day sessions as a team. At the end of the face-to-face session the new Trainers will be asked to provide feedback on EPEC®-Pediatrics as a whole and assess their learning as part of the process. Feedback will be sought using a Knowledge Transfer and Exchange (KTE) Survey completed in paper based format.

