Once Regional Team members have completed their training they will work to deliver aspects of the EPEC®-Pediatrics curriculum to End-Users at their local site. Trainers will be encouraged to think very broadly about who provides care to children with cancer within the institution where they are based, within the local community, and more broadly in the wider geographic area served by the hospital. Education sessions may be offered as part of existing structures (e.g., resident training session, education days for nurses, academic rounds, lunch and learns) or as separate sessions delivered specifically for the study. When End-Users attend an EPEC®-Pediatrics session, they will be provided with a consent form that gives details about our study. If they agree to take part, End-Users will be asked to complete the KTE Survey in hard copy to assess the impact of the session on knowledge transfer. Even if people in attendance do not want to take part in the research aspect of the session they are still welcome to attend. The Trainers who deliver the session will collect the surveys and submit them to the core study team via Research Electronic Data Capture (REDCap™) database, which is a secure, web-based application designed specifically for clinical research [29].

Regional Team members will be asked to complete an Education Roll-out Report on a quarterly basis to provide summary information about the education sessions they have delivered to local End-Users. The Report will be completed verbally with the Project Manager/Principal Investigators (PI) via telephone or Skype and data will be entered into REDCap™.

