Our study design and timelines will allow us to adequately measure the impact of the EPEC®-Pediatrics curriculum roll-out on self-assessed knowledge improvements of health professionals; knowledge transfer and dissemination outcomes; and practice change outcomes, as has been done in the past [20]. However, our study will be the first to examine the impact on a national level. We have chosen a pre- post-test design to evaluate our intervention in terms of its impact on quality of care. A recent systematic review indicated that a train-the-trainer model is effective in improving patient outcomes; however, the length of the intervention and timing of data collection varied widely across studies [22]. Therefore, there is little evidence available to determine an optimal length of the intervention or timing for outcome assessment that could be used to guide a stronger design, such as a cluster randomized controlled trial. It is possible that a longer intervention period and a longer follow-up period for post-test data collection may show greater improvements in patient outcomes. Additionally, though one of the strengths of EPEC®-Pediatrics is the breadth of knowledge covered in the curriculum and the flexibility that Trainers have in choosing which aspects of the curriculum to present to End-Users, this flexibility means that the roll-out may look very different across the participating sites. To address some of the limitations we will explore differences in how the curriculum has been rolled out in each site (e.g., number and type of education sessions, number of End-Users, type and success of QI projects) and whether these differences are associated with any differences in quality of palliative care across sites. This exploration may help to identify some core components of the curriculum that must be included as part of the intervention and may advance the science such that a stronger design could be used in future research to roll-out the curriculum to health professionals who care for children with life-threatening illnesses other than cancer.

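### As described, the Stream 1 instruments cannot show whether 600 distinct End-Users were reached or whether the sessions affected practice

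*Protocol article*

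**What the plan says.** All references are to the protocol article.

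- **Goal (Stream 1, Data analysis).** "Our dissemination goal is to have a minimum of 5 Master Facilitators, 45 Trainers, and 600 End-Users from multiple professional groups across Canada"; the sentence ends by requiring that they "take part in at least one EPEC®-Pediatrics session".
- **Hypothesis (same section).** Trainers and End-Users are expected to report that the sessions were useful, "improved their knowledge related to the topic presented, and had some impact on their practice".
- **Decision rule (same section).** Summaries of the roll-out reports and the KTE Surveys are set against these goals and hypotheses to decide whether they were met.
- **Education Roll-Out Report (Data collection tools).** It is designed to "collect the number of times each EPEC®-Pediatrics module was offered along with the total number of attendees at the session". Regional Teams give it verbally, "on a quarterly basis to provide summary information about the education sessions they have delivered to local End-Users" (Sample and procedure).
- **KTE Survey (Data collection tools; Sample and procedure).** It has demographic items, agreement items on relevance, usefulness and knowledge, and an item on "whether the participant plans to discuss the information provided at the session with colleagues or use the information to make changes in practice". End-Users complete it if they consent, and the Trainers who gave the session collect it. Trainers complete theirs at the end of the face-to-face conference. Attendees who decline the research may still attend.
- **Claims about design.** The Abstract places four areas, the first being self-assessed knowledge, under a pre-post design. The Discussion says of self-assessed knowledge, dissemination and practice change: "Our study design and timelines will allow us to adequately measure the impact".
- **Trainer numbers (Sample and procedure).** "At each of the 16 participating sites, 3 to 5 health professionals will be identified as Regional Team members", and the total is given as n = 45-80.

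**The concern.** The article names both the targets and the two instruments that will settle them, so the instruments should measure what the targets say. In two places they do not.

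First, the End-User goal counts people, while the Report counts attendees session by session. The curriculum has 24 modules, and the settings suggested for teaching (resident sessions, nurses' education days, rounds) draw the same staff repeatedly. Repeat attendance is therefore likely, and no step for removing duplicates is described. The goal could be declared met when far fewer than 600 people had been reached. The Discussion also plans to relate the number of End-Users at each site to care quality, so the same count would mix reach with repetition there.

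Second, the hypothesis speaks of an impact that has happened, but the matching item asks about intention. A report that followed the rule as written could present intention as practice change.

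A related wording point is that a single rating after the session gives a perceived gain in knowledge, not a pre-post difference.

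**Working it through.** **No figure to reproduce.** The 600 is a target. No power, effect size or formula lies behind it.

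**Step 1. People and attendances.** Let N be the number of distinct End-Users, A the attendances summed over sessions, and m the mean number of sessions per person. Then A = N × m, so N = A / m. The documents do not give m; the values below are assumptions to show the range.

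| m (assumed) | People behind 600 attendances (600 / m) | Attendances that 600 people produce (600 × m) |
|---|---|---|
| 1 | 600 | 600 |
| 1.25 | 480 | 750 |
| 1.5 | 400 | 900 |
| 2 | 300 | 1200 |
| 3 | 200 | 1800 |

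Summed attendances equal people only at m = 1, that is, if nobody attends twice.

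**Step 2. Can the KTE Survey supply N instead?** If c is the share of attendances that yield a completed form, the number of forms is N × m × c. Repeat attendance pushes the count above N, and refusal pushes it below. The person-level items named are role, designation, organization type and province, which do not separate one person from another. Neither m nor c can be recovered from the instruments as described, so even the direction of the error is unknown.

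**Step 3. Practice: target against instrument.**

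| | Hypothesis | Item described |
|---|---|---|
| Content | the session had an effect on practice | the participant plans to discuss the content or use it to change practice |
| Time | after practice could change | on a form tied to the session |

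No later KTE Survey is described, and the Roll-Out Report is not described as holding data on End-Users' practice. Stream 2 does measure practice change, but through the Regional Teams' quality improvement projects and not in End-Users' own practice.

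**Step 4. Knowledge.** The survey asks for agreement that knowledge increased. No rating before the session is described in Stream 1. The baseline and repeat collections set out in the article belong to Stream 3.

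**Step 5. Trainer range.** 16 × 3 = 48 and 16 × 5 = 80, against the printed 45-80. The upper end uses 16 sites; the lower end equals 15 × 3 = 45.

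**The case against.** **The forms are not reproduced.** The demographic items are given as examples, the figure of dissemination goals is not shown, and the article never says outright that session totals will be summed to reach 600. An identifier or first-attendance item may exist. This stands as a limit: the point applies to the instruments as described. It does not remove the point, because the article fixes the decision rule and the two sources, and describes no route from attendees to people.

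**A reader might infer that none of Stream 1's goals can be judged.** The document does not support that. Master Facilitators and Trainers are identified individuals and can be counted. Usefulness and improved knowledge match survey items directly, and since participants need only say so, one self-report answers that hypothesis.

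**A reader might infer that the research question on practice change goes unanswered.** It does not. That question belongs to Stream 2, which has its own quarterly report and its own goal of 10 of 16 teams. The clause at issue is one part of a descriptive Stream 1 hypothesis.

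**A reader might take the extreme case, 600 / 24 = 25 people.** This would need every End-User to attend all 24 modules, with 25 / 16 ≈ 1.6 End-Users per site. Trainers are to deliver only parts of the curriculum, so this is not a realistic figure. The 200 people at m = 3 is likewise an illustration, not an estimate.

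**Timing for Trainers.** They finish 19 online modules before the conference, so some change in practice could precede their survey. That is fair, but the item described still asks about plans.

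**A reader might call the goal of 45 Trainers an error.** A minimum goal may sit below the 48 expected. Only the range n = 45-80 disagrees with the stated team sizes.

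**The pre-post wording.** The Abstract sentence may be loose umbrella wording, and the Discussion ties the choice of pre-post design to quality of care. That makes it a matter of wording and not a flaw in the Stream 1 analysis.

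**Conclusion.** The point holds for two Stream 1 targets, as the instruments are described. The 600 End-User goal is stated in people and collected in attendances, so a summed total overstates people by the factor m: no error at m = 1, and 480, 300 or 200 people behind 600 attendances at assumed means of 1.25, 2 or 3. The practice hypothesis is matched only to an item on plans, so the data can support a statement about intention and no more.

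Two smaller matters follow. With no pre-measure described in Stream 1, the knowledge outcome is a perceived gain. The range n = 45-80 should be reconciled with 48-80.

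The conclusion rests on the article's account of the two forms. If the full KTE Survey or the attendance records already identify repeat attendees, the first part falls away. No significance test or power figure is affected. What is at stake is what the study may claim about its reach and about practice.

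**What to change.** 1. **End-User count.** Add one tick-box to a sign-in sheet for everyone present, whether or not they consent to the survey: is this your first EPEC-Pediatrics session in this project? Carry the number of first-time attendees into the quarterly Report and judge the 600 goal on it. Otherwise, restate the goal as 600 attendances. Use the same person count for the site-level exploration described in the Discussion.
2. **Practice hypothesis.** Reword it as intention to change practice. Keeping a claim of actual impact would need a measurement some time after the session.
3. **Knowledge outcome.** In the Abstract and the Discussion, describe it as perceived gain reported after the session, and limit the pre-post label to the outcomes that have a baseline.
4. **Trainer range.** Change n = 45-80 to 48-80, or say why fewer than 48 might take part. The minimum goal of 45 can stay.

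The cost is one tick-box and some edits to wording. The tick-box depends on attendees' memory, and the stated conclusions on practice and knowledge become slightly weaker.

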**Fig. 1 Fig1:**
[figure not shown]
Dissemination Goals

### Stream 2 - Practice change outcomes

Data collection and analysis in Stream 2 will address the impact of EPEC®-Pediatrics on practice change outcomes; namely how many of the Regional Teams initiate QI projects and achieve their practice change goals.

#### Procedure

Regional Teams at each of the 16 sites will be encouraged to complete and report on a QI project related to the overall goals of the study to improve palliative care for children with cancer. Teams may choose to use one of the TIPS Kits that are available as part of the project, or they may choose to do their own project. The EPEC®-Pediatrics curriculum currently includes one TIPS Kit on ‘symptom assessment’, with two additional kits under development related to ‘identifying goals of care’ and ‘bereavement support’. Data will be collected about the QI projects on a quarterly basis through a QI Progress Report. The report will be completed verbally on a quarterly basis with the Project Manager/PIs via telephone or Skype and data will be entered into REDCap™.

#### Data collection tool

The QI Progress Report was developed by the study team to collect information about progress made on the QI projects. Information will be collected about the practice improvement goals, strategies to achieve these goals, a summary of audit and feedback results, plans for the next quarter, as well as successes, challenges and areas for further support.

#### Data analysis

QI Progress Report Data will be summarized descriptively. Our goal is to have at least 10 of the 16 Regional Teams successfully attain the practice improvement goals set in their chosen QI project.

### Stream 3 - Quality of care

Data collection and analysis in Stream 3 will address the impact of EPEC®-Pediatrics on the quality of palliative care provided to children with cancer and their families. Quality of palliative care will be assessed using data from three sources: A) surveys about symptoms, quality of life, and care quality completed by children receiving active treatment and their parents; B) review of health records of deceased patients; and C) surveys with bereaved parents about the quality of their children’s end-of-life care. Baseline data will be collected through each of the 16 pediatric oncology programs from January to April 2015, to provide a cross-sectional view of the quality of palliative care prior to the EPEC®-Pediatrics roll-out. The same data will be collected again from September to November 2016 to determine the impact of the roll-out on care quality.

#### Sample and procedure: A) Surveys during active treatment

Parents of children with a cancer diagnosis who are receiving treatment through one of the 16 pediatric oncology programs in Canada will be invited, along with their child, to complete a survey about symptoms, quality of life, and care quality. Parents will be eligible to take part if the child is less than 19 years of age, has a cancer diagnosis, and they are able to understand and read English or French. Parents will be excluded if the child is disease-free and has not received cancer-directed therapy in the last 3 months or if the health professional involved in their care feels the family should not be approached for research participation at this time (e.g., a recent relapse, difficulty coping with child’s illness, etc.). Children aged seven years or older who meet the same criteria as the parents will be invited to complete their own survey about symptoms and quality of life.

The Parent Survey has been adapted from ‘The Survey About Caring for Children With Cancer’ (SCCC) [9, 31, 32] and the ‘Quality of Children’s End-of-Life Care Instrument’ (QCECI) [33]. The SCCC, developed by one of our co-investigators (JW), is a widely used comprehensive, self-administered survey that evaluates parents’ perceptions of the child’s illness and care quality. It was originally developed from a literature review and focus groups with parents and health professionals to identify key domains, and underwent pretesting to assess content, wording, response burden, and cognitive validity [9, 31, 32]. The QCECI was developed in a similar manner as the SCCC and tested for reliability and validity by one of the co-PIs (KW), with bereaved mothers [33]. It has also been adapted and used with parents prior to the child’s death to assess care quality. The Parent Survey will take approximately 15-30 min to complete.

The Child Survey consists of the ‘Memorial Symptom Assessment Scale’ [25, 26] and the ‘Pediatric Quality of Life Inventory’ (PedsQL™) 4.0 generic module [34] to assess symptoms and quality of life as well as questions asking how often they are asked about symptoms and quality of life by health professionals. The Child Survey will take approximately 15-20 min to complete.

Eligible children and parents will be approached during an inpatient stay or regular clinic visit by their primary nurse or other health professional actively involved in their care to see if they are interested in learning more about our study. If so, the Research Assistant (RA) will meet with the parent and child to provide further information about the study. Assent/consent will be obtained from eligible children and parents. If both parents are present, they will be asked to choose one parent to complete the survey. If the child is less than seven years old or if the child does not wish to complete a survey, the parent will still be asked to participate in the study. The RA will have hard copies of all assent/consent forms available, but the assent/consent forms will also appear in REDCap™ prior to any questions being asked. Submission of the survey signifies assent/consent. Children and parents who agree to take part will be given the option of completing the survey with the RA (i.e., the RA would access REDCap™, read the questions to the participant, and enter the responses), providing an email address where a link to the survey on REDCap™ can be sent, or taking a business card that has the survey link written on it so the participant can complete the survey on their own. Children/adolescents will be offered a certificate of completion for taking part in the study. Eligible children/parents will be approached only once during each data collection period to take part in the study; however, a child/parent who was approached during the pre-test period (Winter 2015) may be approached again during the post-test period (Fall 2016) if they still meet the eligibility criteria. Families who take part in both the pre- and post-testing period will not have their responses linked, as we are interested in cross-sectional data rather than longitudinal.

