In our study, the content of EPEC®-Pediatrics will not be changed; however, four key features will be added to the delivery process based on implementation science [27] to promote sustained improvement in the quality of palliative care for children with cancer and their families. 1) Rather than attending as individuals, Regional Teams of three to five health professionals representing oncology, palliative care, and the community (e.g., home care nurses, community pediatricians) will attend a Train-the-Trainer Conference together in 2015 and work as a team. 2) A second day will be added to the Conference to allow Regional Teams to review data collected in the pre-test period and use those data to develop regional dissemination strategies and plan their QI project. 3) The Research Team developed two additional TIPS Kits to provide a wider choice of QI projects. 4) Ongoing support will be provided by the Research Team for education and QI initiatives throughout the intervention period, 2015 - 2016. Teams will also communicate with each other via a listserv and webinars to share successes and challenges.

The effectiveness of our EPEC®-Pediatrics roll-out will be assessed according to four outcomes. The guiding research questions are: What is the impact of EPEC®-Pediatrics on: 1) the self-assessed knowledge of health professionals who take part in the curriculum; 2) knowledge transfer and dissemination outcomes; 3) practice change outcomes, and 4) the quality of palliative care provided to children with cancer and their families?

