#### Sample and procedure: C) Bereaved parent surveys

During the pre and post-test period, bereaved parents will be invited to complete a survey about the quality of their children’s end-of-life care. Potential participants will be identified according to the following inclusion criteria: 1) Child died following a cancer diagnosis; 2) Child aged 19 years or younger; 3) Parents are able to read English or French. Parents will be excluded if: they requested to have no further contact from the hospital such as for bereavement follow-up support. Bereaved parents will not be approached about the study until at least 6 months have passed since the time of the child’s death. Therefore, in order to achieve the required sample size we will invite parents whose child died during a 2 year window that ends 6 months prior to the end of the pre-test data collection period (e.g. Invitation letters would be sent in January 2015 to bereaved parents whose child died between July 2012 and July 2014) and in an 8 month window that ends 6 months prior to the end of the post-test data collection period (e.g. Invitation letters would be sent in January 2017 to bereaved parents whose child died between December 2015 and July 2016).

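### Active-treatment survey (source A): who may be approached rests on the judgement of staff in the group being trained, so case mix could shift between periods, and the planned model would not correct for it

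*Protocol article*

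**What the plan says.** **Entry to the survey.** Under Stream 3, Sample and procedure: A) Surveys during active treatment, a family is excluded when "the health professional involved in their care feels the family should not be approached for research participation at this time (e.g., a recent relapse"; trouble coping with the illness is the next example. The same section has families first "approached during an inpatient stay or regular clinic visit by their primary nurse or other health professional actively involved in their care". Both steps rest on staff discretion.

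**Who is trained.** Background describes "Regional Teams of three to five health professionals representing oncology, palliative care, and the community". Stream 1, Sample and procedure, says of the local sessions that "Trainers will be encouraged to think very broadly about who provides care to children with cancer within the institution where they are based", and then extends this to the community and the wider region. Stream 1, Data analysis, sets the target: "Our dissemination goal is to have a minimum of 5 Master Facilitators, 45 Trainers, and 600 End-Users from multiple professional groups across Canada".

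**Timing and aim.** Design places about 15 months of roll-out between the pre-test (from January 2015) and the post-test (fall 2016). Background says each module addresses attitudes as well as knowledge and skill, in the hope of changing behaviour.

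**Analysis.** Source A consists of two unlinked cross-sections. Stream 3, Data analysis, regresses each indicator on time point by GEE, allowing for clustering within regions. It names no case-mix covariate. The limitations in the Discussion cover the length of intervention and follow-up and the variation between sites, but not who is surveyed.

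**The concern.** A treating professional's veto is a normal safeguard. It needs attention here because the staff who exercise it belong to the group whose attitudes and behaviour the study sets out to change, and the change is meant to happen between the two surveys. Selection into the sample may therefore lie downstream of the exposure being evaluated.

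Recently relapsed or poorly coping families plausibly report worse symptoms, and the proportion reporting severe symptoms is one of the indicators named under Sample size. If trained staff clear more of these families, the post-test looks worse and a real improvement is partly hidden. If they become more protective, an improvement appears that owes nothing to better care. There is no concurrent control group against which either movement would show.

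**Working it through.** **1. The plan's own figures.** The plan gives no figure for selection. The yardstick is the 15 % difference under Sample size, read here as 15 percentage points. The 200 baseline and 100 post-test records for 80 % power cannot be reproduced uniquely, because no baseline rate is stated. With ICC 0.01 and 16 sites, a design effect of 1 + (300/16 − 1) × 0.01 = 1.1775 gives 79.0 % power for 15 % vs 30 % (two-sided 0.05, pooled chi-square). The stated power is thus reachable at some baseline rates. This has no bearing on selection; the figures serve only as a scale in step 5.

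**2. Assumed inputs (none is in the documents).**
- q, the share of eligible families who are recently relapsed or otherwise hard to approach: 10 to 30 %.
- A, their severe-symptom rate: 50 to 70 %.
- B, the rate in other families: 30 %.
- a, the fraction of hard-to-approach families cleared for approach, which differs by period. All other families are approached.

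**3. Formulas.** Share of hard-to-approach families among those surveyed: s = q·a / (q·a + 1 − q). Apparent rate: s·A + (1 − s)·B. Care, and hence A and B, is held constant, so any movement is artefact.

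**4. Results.** Middle case, q = 0.20, A = 0.60, a rising from 0.20 to 0.80:
- Pre: s = 0.04 / (0.04 + 0.80) = 0.0476; rate = 0.0476 × 0.60 + 0.9524 × 0.30 = 31.4 %.
- Post: s = 0.16 / (0.16 + 0.80) = 0.1667; rate = 0.1667 × 0.60 + 0.8333 × 0.30 = 35.0 %.

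Other scenarios (shifts from unrounded values):

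| q | A | a, pre to post | Apparent rate | Shift (points) |
|---|---|---|---|---|
| 10 % | 50 % | 50 % to 60 % | 31.1 % to 31.2 % | +0.2 |
| 30 % | 70 % | 50 % to 60 % | 37.1 % to 38.2 % | +1.1 |
| 10 % | 50 % | 40 % to 70 % | 30.9 % to 31.4 % | +0.6 |
| 20 % | 60 % | 20 % to 80 % | 31.4 % to 35.0 % | +3.6 |
| 30 % | 70 % | 20 % to 80 % | 33.2 % to 40.2 % | +7.1 |
| 30 % | 70 % | 80 % to 20 % | 40.2 % to 33.2 % | −7.1 |
| 30 % | 60 % | 0 % to 100 % | 30.0 % to 39.0 % | +9.0 |

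The last row is an extreme illustration, not a ceiling: a wider gap between A and B would give more.

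**5. Effect on a test.** Suppose the 200 and 100 apply to source A. Dividing by 1.1775 leaves 169.9 and 84.9 effective records. In the middle case a true 15-point fall (31.4 % to 16.4 %) has 74 % power. With the 3.6-point artefact the expected contrast is 31.4 % to 20.0 %, and power is 49 %.

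**6. Does the stated model remove it?** No. Allowing for clustering corrects standard errors for similarity within a region. It does not make two samples of different composition comparable, and the responses of families surveyed twice are not linked.

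**The case against.** A fair reply is that this is an ordinary ethical safeguard in an openly uncontrolled pre-post study, and that screening logs and sensitivity analyses usually sit in a fuller document. Much of that stands, and it limits the point. Several stronger readings are tempting but unsupported.

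- **That the clinicians who decide are all trained by 2016.** The documents show overlap of groups, not of individuals. The target is 600 End-Users nationally, 600/16 = 37.5 per site, each attending at least one session and some drawn from the community. Nothing says that the nurses who approach families are among them.
- **That the mix is likely to change.** No module in Table 1 concerns approaching families for research. The documents support *could*, not *likely*, and give no direction.
- **That relapse is itself an exclusion.** It is an example of when a professional may judge that a family should not be approached at this time.
- **That the bereaved-parent survey shares the problem.** It excludes parents only where "they requested to have no further contact from the hospital such as for bereavement follow-up support". That is the parents' own request; eligible families are identified through Health Records and no clinician veto is described. The health record reviews take all deaths and are also unaffected.
- **That under-representing hard-pressed families biases the comparison in itself.** If it is the same in both periods it limits generalisability. Only a change in it biases the pre/post contrast.

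What survives is that the article itself states the discretionary rule and an analysis on time point with clustering. The weakness comes from putting the two together, not from a detail left out of a condensed article.

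**Conclusion.** The point holds for source A only. Entry to the active-treatment survey depends on the discretion of a staff group that the intervention targets between the two surveys, so the case mix could differ by period because of the intervention, and the stated GEE would not correct for it.

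Direction and size are unknown. Under the assumed inputs the artefact is about 0.2 to 1.1 points for a small change in clearance, 0.6 to 7.1 points for larger ones, and 9 points in the extreme case. A reader might infer that a planned-size benefit could be reversed. None of these scenarios does that to a true 15-point difference, although smaller true effects could be hidden or imitated. The calculation shows what is possible; it is not evidence that a shift occurred. The case for acting is that the remedy is cheap and the bias cannot otherwise be seen.

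**What to change.** - Keep the clinician's veto, and apply the same exclusion wording in both periods. Rewording it after the baseline survey (January to April 2015) would itself create a pre/post difference in selection.
- Have the research assistant at each site return, for each period, an anonymous count of eligible families by relapsed/not relapsed and by approached/withheld, with the reason for withholding. Use one definition of relapse throughout.
- Record relapse status for each source A respondent.
- Add a stated sensitivity analysis: the pre/post comparison adjusted for relapse status, or weighted so that both periods represent the same eligible relapse mix.
- If baseline counts cannot be recovered, adjust for respondents' relapse status where available, and limit the source A conclusion accordingly.

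**Cost.** A short tally per site and period and one extra analysis, plus whatever notification the site ethics boards require. **Limits.** Weighting on relapse does not address families withheld for difficulty coping, and it fails if no relapsed family was approached in one of the periods. The recorded reasons would at least show how often each situation arose.
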